
Despite the high prevalence of anxiety disorders in adolescents (11–18 years), the potential therapeutic use and anxiolytic effect of OXT (see above), as well as the influence of stress on the endogenous OXT system of children and adolescents, have only been investigated in one study with healthy volunteers by Bernhard et al. [32]. In a standardized laboratory setting the authors demonstrated that the peripheral OXT level increased under psychosocial stress conditions (using the TSST [33]). In addition, this study concluded that low basal OXT levels were associated with greater expression of anxiety and insecurity during stressful situations. Children and adolescents with a primary low basal OXT level showed a greater increase in OXT during the TSST. In contrast, a higher basal OXT level correlated subsequently with less anxiety [32]. Even though childhood experiences influence the regulation of OXT release in adulthood [13], there is no comparable trial investigating the response of the endogenous OXT system to an acute stressor in children and adolescents with psychiatric disorders, in particular, anxiety disorders compared to a control group of same-aged healthy participants without psychiatric diagnoses.

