In the study by Bernhard et al. [32], the salivary cortisol (CORT) concentration was examined as a second neurophysiological parameter of stress reaction. The adrenal cortical hormone CORT is an elementary component of the hypothalamic–pituitary–adrenal (HPA) axis and the endocrinological stress regulation system. A meta-analysis by Cardoso et al. [34] supported the hypothesis that OXT plays an important role in the etiology of HPA dysfunction associated with psychopathology. The detailed interplay of OXT and CORT under stress conditions has rarely been studied [32]. In a human study in 2003, Heinrichs et al. [35] were the first to observe that the combination of i.n. OXT and social support suppressed CORT levels under stress conditions (TSST) and resulted in increased calmness and decreased anxiety. In healthy participants i.n. OXT, as well as natural high baseline OXT concentrations in saliva, appear to be correlated with low CORT response and less anxiety in stressful situations [32, 35, 36]. In contrast, lower baseline OXT was associated with higher CORT levels and greater OXT reactivity [32]. To the best of our knowledge, the only study addressing this relationship in children and adolescents was conducted by Bernhard et al. [32]. In the study, healthy children and adolescents showed an earlier peak of salivary OXT at + 1 min after stress compared to the CORT level at + 10 min after stress. Furthermore, they showed an earlier decrease of OXT to the baseline level compared to CORT after stress exposure was terminated [32]. Based on the earlier OXT peak, the authors assumed that OXT has a regulatory effect on CORT, which may act as a support mechanism during stressful situations [32]. In the present study, we expect a dysregulated interplay between OXT and CORT under stress [34] in children and adolescents suffering from anxiety disorder compared to healthy controls. If children and adolescents with anxiety disorder show a low basal OXT level (see above), there are two possible assumptions on the interplay between OXT and CORT. On the one hand, since low basal OXT levels in healthy participants correlated with a higher increase of saliva OXT and CORT during the TSST [32], we expect participants with anxiety disorder to show less increase of OXT, thereby reflecting a pathological lacking stress-buffering mechanism [15] and a subsequently higher expression of subjective stress and anxiety [35, 37]. On the other hand, because of the HPA axis co-activation and greater stress-induced OXT reactivity associated with faster vagal recovery, Engert et al. [38] rather suggested a “recovery-boosting” than a “reactivity-buffering” effect. With respect to previous research, however, the influence of OXT on the HPA axis under stress has not been fully determined yet, especially regarding clinical populations. Recent findings describe a blunted CORT response to psychosocial stress (TSST) in women with anxiety disorder [39] and patients with panic disorder [40, 41]. These findings led to the hypothesis of a HPA-axis hypo-responsiveness in patients with mental health disorders, promoting high vulnerability during acute stress response. This was also found in studies with adolescents with non-suicidal self-injury (NSSI) [42].

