### Primary hypothesis

It is hypothesized, that the endogenous OXT system of children and adolescents (11–18 years of age) suffering from a clinically diagnosed anxiety disorder is dysregulated. As different types of anxiety disorders in children have been associated with dysregulation of the HPA-axis [43], no differences between different types of anxiety disorders in response to stress are expected. A lower basal OXT level of the experimental group, as well as less OXT release as a response to an acute stressor, is expected, compared to the control group. In both groups, it is assumed that the OXT level peaks and decreases earlier than the CORT level. We expect a negative correlation between basal OXT level and CORT increase in both groups. Basal OXT and OXT increase under stress are expected to correlate positively with subjective stress level (VAS). OXT increase is expected to correlate positively with vagal recovery. In healthy controls, we anticipate a positive correlation between OXT release and CORT release. As described in the background section, in participants with anxiety disorders two controversial hypotheses about the interplay between CORT and OXT under stress will be discussed. First, participants with anxiety disorders might show low OXT increase correlating with high CORT increase reflecting a pathological, lacking stress-buffering effect of OXT. Second, participants with anxiety disorders might show low OXT increase correlating with attenuated CORT response reflecting HPA-axis hypo-responsiveness.

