To assess the relationship between OXT and CORT reactivity, FDR-corrected correlations will be computed between CORT and OXT baseline levels and the increase and recovery measures. In case of significant correlations between CORT and OXT, a linear multiple regression model will be computed with CORT increase as dependent variable and OXT increase, CORT baseline and group as predictors to determine the amount of variance that is explained by OXT increase independently of baseline CORT. An additional regression model will be computed with CORT recovery as dependent variable and OXT increase and CORT increase as predictors. Effect sizes will be reported using Cohen’s *d* with 0.2 being considered a small, 0.5 a medium and 0.8 a large effect.

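### The regression of CORT increase on OXT increase leaves out basal OXT, so its OXT-increase coefficient can partly reflect basal OXT rather than release

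*Protocol article*

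**What the plan says.** The Statistical analysis section first tests simple associations: "FDR-corrected correlations will be computed between CORT and OXT baseline levels and the increase and recovery measures". If CORT and OXT are significantly correlated, "a linear multiple regression model will be computed with CORT increase as dependent variable and OXT increase, CORT baseline and group as predictors". The stated aim is "to determine the amount of variance that is explained by OXT increase independently of baseline CORT". A second model follows: "An additional regression model will be computed with CORT recovery as dependent variable and OXT increase and CORT increase as predictors". Basal OXT is a predictor in neither.

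The same section defines increase in two ways: by area under the curve, without saying whether total or relative to baseline, and by a delta score from the baseline measure to the highest value.

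On basal OXT, the Background reports of healthy volunteers that "Children and adolescents with a primary low basal OXT level showed a greater increase in OXT during the TSST". It also says that "lower baseline OXT was associated with higher CORT levels and greater OXT reactivity", and it builds an argument on this: "since low basal OXT levels in healthy participants correlated with a higher increase of saliva OXT and CORT during the TSST". The Primary hypothesis then states for this study: "We expect a negative correlation between basal OXT level and CORT increase in both groups".

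**The concern.** By the article's own account, basal OXT is measured before the stressor and runs in the same (negative) direction with both the predictor of interest and the outcome. A variable placed like that confounds the regression slope if it is left out. Two negative links multiply to a positive one, so OXT increase can earn a positive coefficient and a share of explained variance even if release itself has no link to CORT increase.

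The planned covariates do not remove this. CORT baseline is a different variable. The group term takes out mean differences between patients and controls, but not the association of basal OXT with the two increases within a group.

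The relation between CORT and OXT under stress is the third main question under Objectives, and the Discussion says that a correlation between the two would suggest that OXT may influence CORT release. A reader will take the regression as the adjusted answer to that question. It should therefore be able to tell release apart from the basal level.

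**Working it through.** The article attaches no coefficient, power or sample size to this regression, so there is no stated figure to reproduce. The check is omitted-variable algebra followed by simulation.

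**Inputs from the article.** N = 64, 32 per group, significance level 0.05 (Power calculation); the predictor list (Statistical analysis); the signs of the two links (Background, Primary hypothesis).

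**Inputs assumed.** The sizes of the correlations, which the article does not give, are taken from 0.2 to 0.6 in absolute value. Tests are two-sided. CORT baseline is unrelated to the other variables unless stated.

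**Algebra.** On standardised variables, let corr(basal OXT, OXT increase) = -a and corr(basal OXT, CORT increase) = -b, with no direct link from OXT increase to CORT increase. The expected OXT-increase coefficient without basal OXT is (-a)(-b) = +ab, and the variance credited to OXT increase is (ab)². With a = b = r:

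- r = 0.2: 0.04, variance 0.2%
- r = 0.3: 0.09, variance 0.8%
- r = 0.4: 0.16, variance 2.6%
- r = 0.5: 0.25, variance 6.3%
- r = 0.6: 0.36, variance 13.0%

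If the link between basal OXT and OXT increase holds in one of two equal groups only, the pooled coefficient is roughly the average of ab and 0, that is ab/2. At r = 0.5 this is 0.125.

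**Simulation.** Basal OXT was drawn as standard normal. Each increase was set to -r times basal OXT plus independent noise scaled to unit variance. CORT increase was regressed on OXT increase, CORT baseline and group, with and without basal OXT, in several thousand trials per setting. Share of trials with a significant OXT-increase coefficient when the direct link is zero:

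| r | Planned model, both links in both groups | Planned model, basal OXT-OXT increase link in controls only | Basal OXT added |
|---|---|---|---|
| 0.2 | about 6% | about 5% | about 5% |
| 0.3 | about 10% | about 6% | about 5% |
| 0.4 | 23-25% | about 9% | about 5% |
| 0.5 | about 50% | about 17% | about 5% |
| 0.6 | about 83% | about 28% | about 5% |

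Keeping CORT baseline in the model helps little. With corr(basal OXT, CORT baseline) = -0.3 and r = 0.5 in both groups, the mean coefficient is 0.23 and the share is 45%.

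**Part of the link is arithmetic.** With delta = peak - baseline, equal standard deviations and baseline-peak correlation ρ, corr(baseline, delta) = -√((1-ρ)/2). For ρ = 0.3, 0.5, 0.7 and 0.9 this is -0.59, -0.50, -0.39 and -0.22. For the delta score, then, a negative link with baseline is to be expected in any group unless peak values are much more variable than baseline values.

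**The precondition.** The table ignores the rule that the regression runs only after significant correlations. A simplified version of that rule was tried: FDR over two correlations, of OXT increase and of basal OXT with CORT increase, using true delta scores with ρ = 0.5. For basal OXT-CORT increase correlations of -0.3, -0.4 and -0.5 it let the regression run in about 62%, 87% and 98% of trials. Within those, OXT increase was significant in about 33%, 39% and 52%, against 5% to 6% with basal OXT included. The rule offers no protection, because the predicted correlation of basal OXT with CORT increase can itself satisfy it.

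**The case against.** The best defence is that the model does what its sentence promises. The aim is limited to independence from baseline CORT, and CORT baseline is in the model. Basal OXT is not ignored either, since it is correlated separately with the increase and recovery measures. This stands: the article does not break its own stated aim. But separate correlations adjust nothing, so they cannot show how much of the OXT-increase coefficient belongs to basal OXT.

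Three stronger readings are tempting, and the article does not support them.

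- A reader might infer that the model would falsely confirm the predicted positive correlation between OXT and CORT release in controls. That prediction is a plain correlation. The regression pools both groups without a group-by-OXT interaction, so it does not test a control-only claim. If basal OXT drives both increases, the two increases really are correlated (at r² in the simulation), and the prediction would be true.
- A reader might infer a bias against the pattern of low OXT increase with high CORT increase in patients. The model estimates no patient slope. The observed link between basal OXT and OXT increase comes from healthy children. For patients the article expects a lower basal level together with less release, and states no correlation between the two within that group.
- A reader might see the same fault in the CORT-recovery model. It too lacks basal OXT, and it lacks CORT baseline, but it already contains CORT increase, which may absorb part of the confounding. No direction or size of bias has been shown for it.

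Two further limits stand. The positive direction applies to baseline-corrected measures (the delta score, or an area relative to baseline). A total area under the curve relates differently to baseline, and the article does not say which is meant. Adding basal OXT also changes the question slightly, as set out in the fix.

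**Conclusion.** The point holds in a limited form. The predictor list omits a variable that the article itself ties to both sides of the regression and that is built into one of the two increase measures. For baseline-corrected increases, the pooled OXT-increase coefficient and its explained variance cannot be read as the contribution of release apart from the basal level.

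How much this matters cannot be settled from the article. At correlations near 0.2 the effect is negligible. At 0.5 the chance of a significant coefficient without any direct link is about 50% if both links hold in everyone, and about 17% if the link between basal OXT and OXT increase is confined to controls. These figures assume linear relations, equal correlations on the two sides, no direct link and 64 complete participants. The term false positive applies here only to a direct link given basal OXT.

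It is a worthwhile improvement to a conditional analysis, using data already planned for collection. It does not show that a stated hypothesis would be wrongly confirmed.

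**What to change.** Add basal OXT as a predictor in the CORT-increase regression. Report the variance explained by OXT increase as the increment over a model that already holds basal OXT, CORT baseline and group. Show the model with and without basal OXT, so that the reader can see how far the coefficient moves.

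Say what the adjusted coefficient means. For the delta score, β₁(peak - baseline) + β₂·baseline = β₁·peak + (β₂ - β₁)·baseline. The adjusted OXT-increase coefficient is thus that of peak OXT given baseline, provided both terms use the same baseline sample. State also which area-under-the-curve measure enters the regression.

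A version of the CORT-recovery model with basal OXT and CORT baseline can be run in parallel as an optional sensitivity check.

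The cost is a change of wording and one degree of freedom. If both links hold in both groups, the standard error grows slightly. With a = b = r, the ratio with to without basal OXT is about 1/√(1 - r⁴), which at r = 0.5 is 1/√0.9375 = 1.03.

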### Safety report

All participants will be informed in advance where to seek help for mental health problems during the procedure and that they can withdraw their consent for participating at any time. Because communication with strangers could induce increased stress levels, especially for anxious patients, participants may feel overburdened and symptoms of anxiety may be intensified during the stress test. If patients are unable to calm down through positive encouragement, the study will be terminated.

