## Methods/design

### Design

The present trial is a single-center experimental observational study with a matched control group. An experimental group of children and adolescents with diagnosed anxiety disorder according to the criteria of the Diagnostic and Statistical Manual of Mental Disorders-IV (DSM-IV) and International Statistical Classification of Diseases and Related Health Problems-10 (ICD-10) will be compared to a matched control group of same-aged healthy children and adolescents. The procedure applies to both groups. Psychometric assessment, hormone assay, as well as physiological measurements (heart rate) will be investigated. The study protocol conforms to the Standard Protocol Items: Recommendations for interventional Trials (SPIRIT) checklist (See Additional file 1).

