### Physiological measures and stress challenge

To minimize the effects of hormone fluctuations caused by the circadian rhythm [32], all participants will start the 2.5 h experimental test session (T2, see Fig. 1) at the same time in the afternoon (4:00 pm). Females who have begun menstruation will be tested in the luteal phase (time after ovulation) of their menstrual cycle, since the CORT stress response of females is more similar to the male reaction in the luteal phase than in the follicular phase [32, 59]. The onset of the female participants' ovulation and the pubertal development will be assessed using the German adaptation [60] of the self-report Pubertal Development Scale [61]. However, in previous studies, no main effect of sex for OXT levels in adolescents was found [32, 62]. Still, to minimize the effect of age and pubertal development [62, 63] both groups will be matched according to pubertal status [61].

At the end of T1, participants and their parents/legal guardians will be instructed to take one saliva sample by themselves at home within a relaxing atmosphere (T2a) and at least one hour after their last food intake. They will be asked to take the sample two days in advance of T2 in the afternoon, at the same time as the experimental test session (T2) takes place (4:00 pm). This will constitute the baseline salivary OXT and CORT level before the experimental test procedure (T2) will be conducted. The experiment will start with a 60 min relaxation period (T2a) to minimize external effects caused by previous food/drink intake, smoking cigarettes or stressful situations. During the experiment, participants will only be allowed to drink water [32]. Participants will be situated in a separate room (Room A) with relaxing material (reading, painting, puzzle, music). After 1 h (− 1 min before TSST start), the first salivary OXT and CORT level will be measured.

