Upon completion of the TSST, participants will be seated in room A, thereby ending the stressful situation (T2c). To investigate the individual progression of coping with stress of each participant, no relaxing materials will be provided. Saliva samples will be taken at + 1, 5, 10, 20, 40 and 60 min after completing the tasks using Salivette^®^ (Sarstedt, Germany) collection devices and stored at − 20 °C until biochemical analysis. Salivary CORT will be measured at the laboratory of the Department of Biopsychology, Technical University of Dresden, Germany. Salivary OXT will be quantified by radioimmunoassay (RIAgnosis, Sinzing, Germany). In order to monitor the stress reaction during the procedure, heart rate will be recorded by an Ecg Sensor (EcgMove4, movisens, Germany) fixed with adhesive electrodes at the chest of each participant. Simultaneously to the physiological assessments, subjective levels of perceived stress, anxiety, insecurity and tension will be investigated using the Visual Analogue Scale (VAS) (Scale from 0 = feeling not stressed/anxious/insecure/tense at all to 100 = feeling highly stressed/anxious/insecure/tense, for more details see Hellhammer and Schubert, 2012 [37]) at 9 different time points [32]. In the relaxation period after the TSST, the experimenter will provide participants with positive feedback on their performance and the information that no video recording was made [32]. Finally, a clinical psychologist or doctor in charge will be available to talk in detail with the study participants and their legal guardians about the test procedure. He will also be available for advice/counseling if needed. See Fig. 2 for an overview of the test procedure.

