### Statistical analysis

To ensure objectivity the data will be assessed in accordance with the current standards of empirical research. The collected data will be evaluated using SPSS 25.0 (IBM Corp. Released 2017. IBM SPSS Statistics for Windows, Version 25.0. Armonk, NY: IBM Corp.). Using $$x^{2}$$—test for discrete analysis of variance (ANOVA) for continuous variables with group and gender as inter-subject factors, the demographic and psychometric data will be evaluated. The measured OXT and CORT levels will be transformed to achieve normal distribution. Correlations between psychological VAS ratings and OXT and CORT will be explored through Pearson correlations in case of normally distributed data and through Kendall’s τ otherwise. As correlation between OXT and CORT is expected, a rmMANOVA (repeated measures Multivariate Analysis of Variance) will be conducted to test the effects of time as a within-subject factor and group as a between-subject factor on OXT and CORT reactivity. In case of correlation between OXT, CORT and VAS ratings, VAS ratings will be included into the rmMANOVA, otherwise separate ANOVAs with the between-subject factor group and within-subject factor time will be conducted. In case of significant main effects or interactions, False Discovery Rate (FDR) [66] corrected post-hoc tests will be performed. Exploratory post-hoc analyses with FDR corrected p-values testing for effects of sex and age on OXT and CORT reactivity will also be conducted.

OXT and CORT increase will be calculated through area under the curve (AUC) analyses as described in Pruessner et al. [67]. Additionally, delta scores will be computed between the OXT and CORT baseline measure and the highest value for a measure of increase [68, 69] and between the highest OXT and CORT value and the lowest value after stress for a measure of recovery [70]. To determine group differences between OXT and CORT baseline, increase and recovery, MANOVAs will be computed with group as a between-subject factor and sex as a within-subject factor. In exploratory analyses, anxiety and depressive symptomatology scores will be included as covariates. As previous research has identified an effect of contraceptives on OXT baseline levels [38] a separate analysis will be run on female participants.

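### Stopping the study for patients who cannot calm down may remove post-stress data selectively, and the planned MANOVAs could then also drop those patients from the basal oxytocin comparison

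*Protocol article*

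**What the plan says.** The Safety report expects distress in the test situation, above all in anxious patients: "participants may feel overburdened and symptoms of anxiety may be intensified during the stress test". Its response is encouragement first, and then: "If patients are unable to calm down through positive encouragement, the study will be terminated". I read this as ending that participant's session, not the whole trial.

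Physiological measures and stress challenge fixes the sampling. One sample is taken at home two days earlier. In the laboratory, "After 1 h (− 1 min before TSST start), the first salivary OXT and CORT level will be measured", and after the test, "Saliva samples will be taken at + 1, 5, 10, 20, 40 and 60 min after completing the tasks". That makes eight samples, two before and six after the stressor.

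Statistical analysis plans a repeated-measures MANOVA with time and group for oxytocin (OXT) and cortisol (CORT) reactivity. It adds: "To determine group differences between OXT and CORT baseline, increase and recovery, MANOVAs will be computed". Power calculation describes one additional MANOVA on basal OXT together with OXT increase, and this is the calculation that set the sample size of 64. Objectives lists the basal OXT difference as the first of three main questions.

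**The concern.** Whether a participant supplies post-stress samples may depend on two things the study compares or measures: group, because distress is expected mainly in patients, and the strength of the reaction to the stressor. Loss of that kind can move the group contrast, and recruiting more participants does not correct it.

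The stated analyses make the consequence larger than it has to be. A repeated-measures MANOVA discards the whole series of anyone with a gap. A joint MANOVA of baseline with increase and recovery discards the baseline too. A primary comparison resting on samples taken before the stressor could therefore lose patients because of what happened during it.

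A second, smaller matter is encouragement. If it is given while the test is running and mainly to patients, the stressor is not the same in both groups, and nothing in the record would show it unless it is written down at the session.

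**Working it through.** **1. What a stopped patient contributes.**

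| When the session ends | Samples available | Repeated-measures MANOVA (8 time points) | Increase and recovery scores | Basal level |
|---|---|---|---|---|
| During the test | 2 of 8 (home, −1 min) | Excluded | Recovery cannot be computed; an increase would rest on the −1 min sample alone and would not measure a stress response | Available |
| In the hour after, e.g. after +20 min | 6 of 8 (2 + 4) | Excluded | Computable, but from a shortened series | Available |

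The first row assumes that sampling ends with the session. The document does not say so, but all later samples are timed from completion of the tasks.

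**2. Does the basal comparison lose these patients?** The sentence in Statistical analysis uses the plural and can be read as one MANOVA per measure, in which case baseline is unaffected. It can also be read as joint. Power calculation supports the joint reading, since it pairs basal OXT with OXT increase in a single MANOVA. On that reading a patient without a valid increase score is deleted from both.

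**3. Direction.** Three statements bear on it.

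- Primary hypothesis expects less OXT release in patients, and OXT increase to rise with subjective stress. Losing the most distressed patients would then lower the patient mean and widen the expected gap.
- Discussion expects less OXT release to go with more CORT and a stronger subjective stress response. The same loss would then raise the patient mean and narrow the gap.
- Basal OXT has the same problem. Primary hypothesis expects it to correlate positively with subjective stress, while Background reports from the earlier study in healthy children that low basal OXT went with more anxiety.

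For CORT, both a high and an attenuated response in patients are entertained. No sign can be fixed from the document.

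**4. Size, as an illustration only.** Let t be the share of patients stopped and r the correlation between distress and hormone response. Neither is in the protocol. If the most distressed share t of a standard normal distribution is lost, the patient mean moves by −r × φ(c)/(1 − t), with c the upper t-quantile.

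| t | c | φ(c)/(1 − t) | Shift at abs(r) = 0.3 | Shift at abs(r) = 0.5 |
|---|---|---|---|---|
| 5% | 1.645 | 0.1031/0.95 = 0.109 | 0.033 SD | 0.054 SD |
| 10% | 1.282 | 0.1755/0.90 = 0.195 | 0.058 SD | 0.097 SD |
| 20% | 0.842 | 0.2800/0.80 = 0.350 | 0.105 SD | 0.175 SD |

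The shift is downward if r is positive, upward if r is negative, and zero if r = 0.

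**5. Loss of numbers alone.** The 64 was sized on f = 0.25, which for two groups is d = 2 × 0.25 = 0.5. Two-sample t-test power at d = 0.5, two-sided 5%, is 50.4% with 32 against 32 and 48.3% with 29 against 32 (about 10% of patients lost at random). Random loss costs about two percentage points, so the issue is selection. The low starting power is a separate question about the sizing.

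**The case against.** Much of the case on the other side stands. The Safety report does not say how often sessions are stopped, when encouragement is given, or that sampling ends. Its phrase about the stress test describes when symptoms may worsen. A stop in the hour after the test would leave some post-stress samples. The article also condenses a fuller document, so the absence of a missing-data section is not itself a fault. Nor does "The procedure applies to both groups" conflict with the safety rule, which sets no different test for either group.

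A reader might infer three stronger things that the document does not support.

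- *That the contrast is biased towards no difference and power falls accordingly.* This needs distress and OXT response to be negatively related in patients. Primary hypothesis expects the opposite sign, which would exaggerate the difference.
- *That encouragement lowers cortisol.* Background says "social support suppressed CORT levels under stress conditions (TSST) and resulted in increased calmness and decreased anxiety", but the subject of that sentence is social support combined with intranasal OXT. It does not show what encouragement alone does. The planned praise is also a different thing: "In the relaxation period after the TSST, the experimenter will provide participants with positive feedback on their performance", which applies to participants generally.
- *That the basal comparison is lost.* It is affected only under listwise deletion from a joint MANOVA, or if data are destroyed after consent is withdrawn (Procedure). A stop for distress is not in itself a withdrawal of consent.

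What the objection does not remove is the choice of methods. The complete-series analysis and the pairing of basal OXT with increase are stated in the article. They make poor use of a participant whose session ends early.

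**Conclusion.** The point holds as a risk of bias of unknown size and direction. The safety rule may make the loss of post-stress samples depend on group and on the stress reaction. The repeated-measures MANOVA would exclude the patients affected, and a joint MANOVA would also exclude them from the primary basal OXT comparison despite usable samples.

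This rests on three assumptions: that some sessions are in fact stopped, that later samples are then missing, and that SPSS handles the gaps by listwise deletion. If no session is stopped, nothing is lost. The illustrative shifts apply only at the assumed rates and correlations and carry no sign. The safety rule is not in question. The change is worth making because it is cheap and because encouragement not noted at the session cannot be recovered later.

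**What to change.** Leave the safety rule unchanged and amend Statistical analysis and the session form.

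1. Analyse basal OXT and CORT separately from increase and recovery, in every participant with a baseline sample and valid consent, whether or not the stress test was completed.
2. Keep every sample taken. Analyse group by time with a likelihood-based mixed model instead of the complete-case repeated-measures MANOVA. State that it assumes data missing at random. It uses partial series, but it does not remove selection on distress that the observed data do not capture, and a patient with only the two pre-stress samples adds little to the post-stress contrast.
3. Record early stops, with their time, and any encouragement during the test. Report both by group. Add a sensitivity analysis that shifts the missing post-stress values of stopped participants up and down over a stated range, and report whether the conclusion changes. The effect is easy to read: with a share t missing, a shift of δ SD moves the patient mean by t × δ, for example 0.10 × 1 = 0.10 SD. A single worst-case score would not serve, since the adverse direction is not known.

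The cost is one extra form field and a slightly longer analysis section. No further visits or participants are needed.
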